##### Bone mineral density

Musculoskeletal symptoms and bone loss are identified as the two main adverse effects of AIs. One study reported a correlation between AIMSS and osteoporosis (bone fractures)
[17]. In order to investigate the effects of YSJG on bone loss, bone mineral density (BMD) of the L2-L4 region of the spine and hip will be assessed before and after treatment (at weeks 0 and 12).

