### Safety assessments

In order to assess the safety of YSJG, we will perform the following tests on all participants at the screening phase (week 0) and after treatment (week 12): blood routine test, urine routine test, feces routine test, kidney function test, liver function test, estradiol (E2), follicle-stimulating hormone, and serum levels of tumor markers (CEA, CA125, and CA153). In addition, investigators will ask every subject at each visit whether they have experienced any adverse events (AEs) during the study period. If there are any AEs, the investigator will provide appropriate treatment to the subject immediately and record AEs in a dedicated document in the case report form, including its severity and causality with the experimental agent. In the case of serious adverse events (SAEs), the investigator will offer appropriate treatment to the subject immediately and report the event to the Institutional Review Board within 24 hours from the time of recognition. If necessary, blinding will be broken by adequate procedure, and the documented procedure will be kept in the investigator study file.

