### Sample size calculation

As there has been no similar TCM research on AIMSS to date, we calculated sample size according to another AIMSS study that used the same primary outcome measure (BPI-SF)
[18]. From the results of this previous study, the treatment group had a reduction of 1.5 points (the standard deviation was 2.1) on the mean BPI-SF worst pain compared with the control group. Therefore, 34 participants per group were deemed sufficient to achieve 90% power and a (one-sided) 5% significance level in detecting treatment differences. Considering a total withdrawal and dropout rate of 20%, we concluded that a total of 84 patients (42 per arm) would need to be recruited to ensure statistically significant results.

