### Statistical analysis

Efficacy and safety analyses will be conducted according to the intention-to-treat principle. Missing values will be imputed by the last-observation-carried-forward method. All statistical analyses will be performed using Statistical Packages of Social Sciences software (SPSS 18.0, Channel-leadian pharmaceuticals R&D, Co., Ltd; [name]). Statistical significance will be defined as a one-sided *P*-value of <0.05. Demographic, clinical, and outcome variables will be described using means and standard deviations for continuous variables and percentages for categorical variables. The primary analysis will be to compare the mean pain scores from BPI-SF, the WOMAC, and the M-SACRAH and the mean joint stiffness and function scores from the WOMAC and the M-SACRAH between the TCM group and the placebo group. The secondary analysis will be to compare the mean scores from FACT-B and changes in BMD before and after treatment. Student’s t-tests and repeated-measure analyses of variance with a time-interaction term will be used to compare group differences.

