### Data collection and monitoring

This is a 24-week clinical trial, in which participants need to take research medication for 12 weeks, accept a 12-week follow-up, attend five assessment visits, obtain two sets of laboratory tests (safety assessments) and BMD analysis, fill in four sets of questionnaires at each visit, and stop taking other herbal medications (Table 
2).

**Table 2 T2:** Data collection schedule

	**Screening**	**Treatment**			**Follow-up**
Visit number	1	2	3	4	5
Week number	−2 to 0	4	8	12	24
Patient characteristics	✘				
Past history	✘				
AIMSS	✘				
ECOG	✘				
BPI-SF	✘	✘	✘	✘	✘
WOMAC	✘	✘	✘	✘	✘
M-SACRAH	✘	✘	✘	✘	✘
FACT-B	✘	✘	✘	✘	✘
Bone mineral density	✘			✘	
Safety assessment	✘			✘	
Combined medication	✘	✘	✘	✘	✘
Adverse events		✘	✘	✘	✘
Compliance		✘	✘	✘	

AIMSS, aromatase inhibitor-associated musculoskeletal symptoms; BPI-SF, Brief Pain Inventory-Short Form; ECOG, Eastern Cooperative Oncology Group; FACT-B, The Functional Assessment of Cancer Therapy-Breast; M-SACRAH, Modified Score for the Assessment and Quantification of Chronic Rheumatoid Affections of the Hands; WOMAC, Western Ontario and McMaster Universities Osteoarthritis Index.

Beijing Qihuang Medicine Clinical Research Center is responsible for quality control. Censors have regular visits (once a month) to monitor protocol violations, the recruitment rate, AEs and participant compliance.

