## Trial status

The trial is currently enrolling participants.

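### LOCF is stated without exception, but BMD and the laboratory panel are measured only at weeks 0 and 12, so a missing week-12 value becomes a change of exactly zero

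*Protocol article*

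**What the plan says.** Two adjacent sentences in the Statistical analysis section set the rule. The first is "Efficacy and safety analyses will be conducted according to the intention-to-treat principle". The second is "Missing values will be imputed by the last-observation-carried-forward method". Neither names an exception.

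The schedule for the two measures concerned is given in three places:

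- **Safety assessments**, on the laboratory panel: "we will perform the following tests on all participants at the screening phase (week 0) and after treatment (week 12").
- **Bone mineral density**, on the spine and hip scans: "will be assessed before and after treatment (at weeks 0 and 12").
- **Data collection and monitoring**: each participant will "obtain two sets of laboratory tests (safety assessments) and BMD analysis". Table 2 marks both measures at screening and week 12 only.

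No early-withdrawal panel or scan is described. The Statistical analysis section names "changes in BMD before and after treatment" as a secondary comparison. It names no laboratory comparison.

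**The concern.** LOCF needs an earlier post-baseline value if it is to carry anything about treatment. The pain, stiffness, function and quality-of-life questionnaires have such values at weeks 4 and 8. BMD and the laboratory panel have none. Applied as written, the rule takes a patient who was randomized and exposed but not scanned or tested at week 12, and records that nothing changed.

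For BMD this enters a comparison that the plan names. For the laboratory panel, which covers liver and kidney function, estradiol and tumor markers, it enters whatever means or percentages are reported. The Background says the trial should give evidence on safety as well as efficacy. A summary that counts untested patients as unchanged understates the size of any change and overstates how many patients were examined.

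**Working it through.** **Inputs.** From Sample size calculation: difference 1.5, SD 2.1, 90% power, one-sided 5%, 34 per group, 42 per arm, 20% total withdrawal and dropout. From Study design: visits at weeks 0, 4, 8, 12 and 24. From Safety assessments, Bone mineral density and Table 2: laboratory panel and BMD at weeks 0 and 12.

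**Assumptions, not in the document.** Dropout spread evenly over time (middle case only); a 10% rate of new laboratory abnormality; a true between-arm difference of 0.5 SD; missing patients at the same risk as tested ones.

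**1. The plan's own figure.** n per group = 2 × (1.645 + 1.282)² × 2.1² / 1.5² = 33.6, so 34, as stated. For dropout, 34/0.8 = 42.5; the plan uses 42. In the other direction, 20% of 42 = 8.4, leaving 33.6, about 34. The plan therefore allows for about 8 losses per arm over 24 weeks.

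**2. How many could lack week 12.** Timing of dropout is not stated. If all losses fall after week 12, none; if all fall before it, about 8. If spread evenly, 8.4 × 12/24 = 4.2, about 4. Stopping the granules does not by itself mean missing the visit.

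**3. What LOCF inserts.** With values only at weeks 0 and 12, a missing Y12 is replaced by Y0, so the change is Y0 − Y0 = 0.

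**4. Effect on summaries.** Let q = tested/42. The filled mean change is q times the mean in tested patients, and so is the percentage with a new abnormality. The filled variance is qσ² + q(1 − q)μ², so when the mean change μ is small the SD is multiplied by about √q.

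| Missing per arm | Tested | q | Shrinkage | 10% new abnormality shown as | SD multiplied by |
|---|---|---|---|---|---|
| 0 | 42 | 1.000 | 0% | 10.0% | 1.00 |
| 4 | 38 | 0.905 | 10% | 9.0% | 0.95 |
| 8 | 34 | 0.810 | 19% | 8.1% | 0.90 |

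The denominator stays at 42 in every row.

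**5. Effect on the between-arm test, equal missingness.** Simulation with 40,000 runs, 42 per arm, true difference 0.5 SD:

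- 4 filled per arm: difference 0.453, SE 0.208 (ratio 2.18); observed cases 0.50 and 0.229 (ratio 2.18).
- 8 filled per arm: difference 0.405, SE 0.198, mean t 2.05; observed cases 0.50, 0.242 and 2.08.

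Estimate and standard error shrink together, so the test hardly moves.

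**6. Unequal missingness, extreme case.** With 8 missing in one arm and none in the other, a change common to both arms appears as a false difference of 34/42 − 42/42 = −0.19 of that change. The article names bone loss as a main adverse effect of aromatase inhibitors. If both arms lost bone, the arm with more missing scans would seem to have lost less.

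**The case against.** The strongest reply is that the laboratory analysis is inferred. The Statistical analysis section lists its comparisons and no laboratory variable is among them. The LOCF sentence does not itself mention safety, and a condensed article may leave such handling to a full protocol or analysis plan that is not shown. This stands as a limit on the laboratory part. It does not remove the BMD part, because BMD change is named as a comparison. Nor is the point a missing detail: the rule is stated, and followed literally it gives a wrong value.

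The effect is also small. Eight missing per arm requires every dropout to occur by week 12. At 4 missing, an assumed 10% abnormality rate gives 3.8 expected events instead of 4.2, a shift of 1 percentage point against a sampling standard error of √(0.1 × 0.9/42) = 4.6 points. Adverse events are asked about at every visit, so symptomatic harm can still be recorded. For BMD with equal missingness, shrinking a treatment difference is conservative for a superiority claim. All of this stands, and it is why the point is modest.

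A reader might go further and infer that the trial would report too low an upper limit for harm. With no events, the one-sided 95% bound 1 − 0.05^(1/n) is 6.9% at n = 42 but 8.4% at n = 34. The arithmetic is right, but the article plans no confidence limit for harm, only means, standard deviations, percentages and tests, so these bounds describe an analysis that it does not contain.

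**Conclusion.** The point holds in a limited form. As written, the LOCF rule turns a missing week-12 BMD scan into a change of zero in a named secondary comparison. On the plain reading of two adjacent sentences, it does the same in any laboratory safety summary. Mean changes and new-abnormality percentages would shrink by 0 to 19% for 0 to about 8 missing per arm, and by about 10% at 4. Reported SDs and denominators would treat untested patients as observed.

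The range rests on the plan's own 20% dropout figure, with timing unknown. The shrinkage relative to tested patients is plain arithmetic. Reading it as shrinkage from the true value needs untested patients to be like tested ones.

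The documents do not support a claim that the rule distorts the trial's main inference. The primary pain outcome has visits at weeks 4 and 8 and is not affected in this way, and the sample size does not depend on this point. A false BMD difference needs unequal missingness; the 8-versus-0 case only marks the extreme, and nothing in the article predicts it.

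**What to change.** Add one sentence to the Statistical analysis section: LOCF does not apply to measures with a single post-baseline time point. Then:

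- **Laboratory safety data:** report observed week-12 values with the number tested in each arm, and do not use a pre-treatment value as a post-treatment result.
- **BMD:** compare observed week-12 values between arms with adjustment for baseline.

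This adds no visit, test or patient burden. The costs are a smaller denominator, lower apparent precision (in the 0.5 SD illustration with 8 missing per arm, a standard error of 0.242 instead of 0.198) and, for BMD, reliance on a missing-at-random assumption. Some randomized patients would not contribute to the BMD comparison, so the number missing per arm should be shown beside it.

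The Trial status section says "The trial is currently enrolling participants", and the Randomization and blinding section keeps assignments concealed until the study ends. The change can therefore be made without knowledge of results and applied to all patients alike. If the full protocol or analysis plan already limits LOCF to the questionnaire scores, only the article's wording needs aligning.

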**Methods/design:**

To determine whether the traditional Chinese medicine *Yi Shen Jian Gu* granules could effectively manage AIMSS we will conduct a multicenter, randomized, double-blind, placebo-controlled clinical trial. Patients experiencing musculoskeletal symptoms after taking AIs will be enrolled and treated with traditional Chinese medicine or placebo for 12 weeks. The primary outcome measures include Brief Pain Inventory-Short Form, Western Ontario and McMaster Universities Osteoarthritis Index, and Modified Score for the Assessment and Quantification of Chronic Rheumatoid Affections of the Hands, which will be obtained at baseline and at 4, 8, 12 and 24 weeks.

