### Outcome measures

#### Primary outcome measure

As pain is the most common complaint of AIMSS, we selected the Brief Pain Inventory-Short Form (BPI-SF) as the primary outcome measure to evaluate general pain. The BPI-SF, created by the Pain Research Group, is a 14-item questionnaire to measure both the intensity of pain as well as the interference of pain in the patient’s life on a scale ranging from 0 to 10.

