#### Secondary outcome measures

##### Quality of life instruments

The Western Ontario and McMaster Universities Osteoarthritis Index (WOMAC) is a patient-reported outcome measure for assessing osteoarthritis of the knees or hips. It consists of 24 questions (5 pain, 2 stiffness, and 17 physical function) and can be completed in less than 5 minutes. We selected the WOMAC index to assess joint pain, stiffness, and functional status in the knees.

The Modified Score for the Assessment and Quantification of Chronic Rheumatoid Affections of the Hands (M-SACRAH) consists of three domains assessing pain, stiffness, and functional status in patients suffering from hand osteoarthritis and rheumatoid arthritis, answered on 100-mm visual analog scales. We selected the M-SACRAH to assess joint pain, stiffness, and functional status in the hands.

The Functional Assessment of Cancer Therapy-Breast (FACT-B), a quality of life instrument to assess the well-being of cancer patients, measures physical, social/family, emotional, and functional well-being as well as additional concerns commonly reported in breast cancer patients. The FACT-B scale has five response levels (ranging from ‘not at all’ to ‘very much’). Changes in the scores on these scales before and after intervention will be compared between the TCM group and the placebo group.

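### The primary endpoint is designated inconsistently (BPI-SF alone in some sections, seven scores on three instruments in another), so the text does not fix which result decides the trial

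*Protocol article*

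**What the plan says.** The protocol article classifies the same instruments in two ways.

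**BPI-SF as the only primary outcome**
- Outcome measures, Primary outcome measure: "we selected the Brief Pain Inventory-Short Form (BPI-SF) as the primary outcome measure to evaluate general pain".
- WOMAC and M-SACRAH come under the heading "Secondary outcome measures". There the role of WOMAC is described as: "We selected the WOMAC index to assess joint pain, stiffness, and functional status in the knees".
- Sample size calculation: refers to BPI-SF as the primary measure and takes its planning difference "on the mean BPI-SF worst pain compared with the control group".

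**Three instruments as primary**
- Abstract, Methods/design: "The primary outcome measures include Brief Pain Inventory-Short Form, Western Ontario and McMaster Universities Osteoarthritis Index, and Modified Score" (the M-SACRAH).
- Statistical analysis: "The primary analysis will be to compare the mean pain scores from BPI-SF, the WOMAC, and the M-SACRAH", together with "the mean joint stiffness and function scores from the WOMAC and the M-SACRAH between the TCM group and the placebo group". The secondary analysis in that section contains only FACT-B and bone mineral density.

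The Statistical analysis section sets one significance threshold, one-sided P below 0.05. It does not say which of the scores listed as primary, or how many of them, must reach it.

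**The concern.** A reader of Outcome measures would say that the trial stands or falls on BPI-SF. A reader of Statistical analysis would say that seven scores carry equal primary status. Both cannot be right, and the choice determines what the stated 5% error rate and 90% power refer to.

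The powered quantity is also hard to find in the analysis. The sample size uses worst pain, a single BPI-SF item. The primary analysis refers only to mean pain scores from an instrument that the article describes as having 14 items covering both intensity and interference.

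At stake is the main conclusion. If the seven scores gave mixed results, the document would support calling the trial positive under one section and negative under another.

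**Working it through.** **1. The plan's own sample size.** Inputs from Sample size calculation: difference 1.5, SD 2.1, one-sided alpha 0.05, power 90%, equal arms.

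n per arm = 2 × (1.645 + 1.282)² × (2.1/1.5)² = 2 × 8.564 × 1.96 = 33.6, so 34. This matches the article. Power at 34 per arm is Φ(1.5/(2.1 × √(2/34)) − 1.645) = Φ(2.945 − 1.645) = 90.3%, or 89.8% by the noncentral t distribution. The figure is correct for one endpoint tested once. With 20% dropout, 68/0.8 = 85 against the stated 84, a difference that does not matter here.

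**2. Count of primary comparisons in Statistical analysis.** Pain on three instruments (3), stiffness on WOMAC and M-SACRAH (2), function on WOMAC and M-SACRAH (2): 3 + 2 + 2 = 7.

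**3. What follows under each possible decision rule.** The article states none, so each is worked out.

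*(a) Any one significant score counts as success.* With independent scores and no true effect on any of them, the chance of at least one false positive is 1 − 0.95⁷ = 0.302. The scores come from the same patients and will be correlated. The article gives no correlation, so a common value ρ is assumed and varied:

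P(at least one) = 1 − ∫ φ(x) · Φ((1.645 − √ρ·x)/√(1 − ρ))⁷ dx

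| Assumed ρ | Chance of at least one false positive | Multiple of 5% |
|---|---|---|
| 0 | 30.2% | 6.0 |
| 0.3 | 24.5% | 4.9 |
| 0.5 | 20.3% | 4.1 |
| 0.7 | 15.9% | 3.2 |
| 0.8 | 13.4% | 2.7 |
| 0.9 | 10.5% | 2.1 |

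*(b) All seven scores must be significant.* The chance that all seven are falsely significant cannot exceed 5%, so the error rate is not inflated. The power to win on all seven cannot exceed the power of the weakest score. The article gives a difference and SD for worst pain only, so the 90% does not describe this rule.

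*(c) BPI-SF worst pain alone decides.* There is one test at one-sided 5%, and the 34 per arm and 90% power apply as stated.

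**4. Which sections fit which rule.** Primary outcome measure, Secondary outcome measures and Sample size calculation fit (c). The abstract and Statistical analysis name more than one primary measure, which does not fit (c), and they do not choose between (a) and (b).

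**The case against.** The strongest reply is that no section says one significant score out of seven makes the trial positive. Statistical analysis lists comparisons and a threshold, not a success criterion, and under rules (b) or (c) the error rate stays at 5%. This stands. A reader might infer that the false-positive rate simply is several times 5%, or that the winning score will be picked after unblinding. The document supports neither as a statement of fact. It describes no such selection, and the article keeps statisticians blinded.

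A second reply is that an article condenses a fuller protocol, so a testing hierarchy or multiplicity rule may sit in a document not shown. That also stands, and the absence of such a rule is not the point here. Condensation does not explain why the same two instruments are secondary in one section and primary in another.

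Third, subscales of one questionnaire may correlate strongly, so 30% is a ceiling. This is right, and at 0.9 the figure is about twice nominal.

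Two larger figures are also tempting but are not relied on:
- Counting each score at all four post-baseline visits gives 7 × 4 = 28 tests. This assumes separate testing at each visit, whereas the section names t-tests and repeated-measures analysis of variance without assigning them to visits.
- A Bonferroni split over seven scores gives about 67% power at 34 per arm. That is the power of one named score. Applying it to WOMAC or M-SACRAH would borrow the worst-pain effect for scores that have no planning values.

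**Conclusion.** The inconsistency is explicit and affects the trial's main conclusion. BPI-SF is the sole primary outcome in Outcome measures and is the basis of the sample size. Three instruments are primary in the abstract, and seven scores are primary in Statistical analysis. The sample size itself is sound for the single endpoint that it was computed for.

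The size of the problem is conditional. Under an any-one-counts rule, which the document does not state, the false-positive chance would be 30% for independent scores and about 24%, 20%, 16%, 13% and 10% at assumed common correlations of 0.3, 0.5, 0.7, 0.8 and 0.9. Under an all-must-succeed rule the cost would fall on power instead. With BPI-SF worst pain alone deciding, the planned 5% and 90% hold. The firm conclusion is that the text does not settle which of these applies, and it must do so before unblinding.

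**What to change.** Bring the abstract and Statistical analysis into line with Primary outcome measure, Secondary outcome measures and Sample size calculation:

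- Name BPI-SF worst pain as the single primary endpoint in every section, at one prespecified time point. Week 12, the end of treatment, is the natural choice. Sample size calculation states no week, so this has to be a deliberate decision and cannot be read off the existing text.
- Move the WOMAC and M-SACRAH pain, stiffness and function scores to secondary. Test them only if the primary result is significant, in a fixed order or with Holm's procedure.
- Label other scores and visits as descriptive.

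This keeps the one-sided error rate for the primary conclusion at 5% and leaves the sample size of 84 unchanged. No extra data are needed. The article reports that the trial is enrolling and that assignments stay concealed until the study is complete, so the change can still be made credibly. The cost is a protocol amendment if the approved protocol carries the Statistical analysis wording. Claims on WOMAC and M-SACRAH also become conditional on the primary result.

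### No baseline adjustment is stated for the t-tests or the repeated-measures ANOVA although every endpoint has a baseline value, and two sections disagree on mean versus change scores for WOMAC, M-SACRAH and FACT-B

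*Protocol article*

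**What the plan says.** The Statistical analysis section names two methods without ranking them: Student's t-tests, and "repeated-measure analyses of variance with a time-interaction term will be used to compare group differences". It names no baseline covariate and does not say whether the screening visit is a level of time in the ANOVA.

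The response variable differs between sections:

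- **Quality of life instruments** (under Secondary outcome measures), closing the description of WOMAC, M-SACRAH and FACT-B: "Changes in the scores on these scales before and after intervention will be compared between the TCM group and the placebo group".
- **Statistical analysis**, primary analysis: mean pain scores from BPI-SF, WOMAC and M-SACRAH, and mean stiffness and function scores from the last two.
- **Statistical analysis**, secondary analysis: "The secondary analysis will be to compare the mean scores from FACT-B and changes in BMD before and after treatment".

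Baseline data are complete by design. Patients "fill in four sets of questionnaires at each visit", and Table 2 ticks all four questionnaires and BMD at screening. A BPI-SF worst pain score of at least 3 is also an entry criterion (Table 1).

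**The concern.** A t-test on follow-up scores ignores the baseline. A t-test on changes subtracts all of it, which over-corrects whenever the regression of follow-up on baseline has a slope below 1. Repeated-measures ANOVA does not settle the matter. If screening is a level of time, the group-by-time term is in effect a comparison of changes; if it is not, the baseline goes unused.

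Two things are at stake. The trial gives up precision it has already paid for, and its estimates remain exposed to chance baseline differences. And for three instruments the article defines two response variables that have different variances and react in opposite directions to a baseline imbalance. WOMAC and M-SACRAH belong to what the Statistical analysis section calls the primary analysis, so the disagreement is not confined to minor endpoints.

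**Working it through.** **Inputs.** From Sample size calculation: "the treatment group had a reduction of 1.5 points (the standard deviation was 2.1) on the mean BPI-SF worst pain", and "34 participants per group were deemed sufficient to achieve 90% power and a (one-sided) 5% significance level". The article does not say whether 2.1 is the SD of a score or of a change, so both readings are shown. It gives no baseline-to-follow-up correlation ρ; 0.3, 0.5 and 0.7 are assumed.

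**Step 1: the plan's own figure.** n per arm = 2 × [2.1 × (1.645 + 1.282) / 1.5]² = 33.57, rounded up to 34, with power 90.3% by the normal approximation (89.8% by the exact t distribution). The stated 34 is therefore an unadjusted one-sided comparison. For 20% dropout, 33.57 / 0.8 = 41.96, or 42 per arm, which matches "a total of 84 patients (42 per arm) would need to be recruited". (Starting from the rounded figure, 68 / 0.8 = 85, a difference of one patient.)

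**Step 2: variance relative to the mean-score t-test**, taking equal variances at both times.

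| Analysis | Formula | ρ = 0.3 | ρ = 0.5 | ρ = 0.7 |
|---|---|---|---|---|
| Mean score | 1 | 1.00 | 1.00 | 1.00 |
| Change score | 2(1 − ρ) | 1.40 | 1.00 | 0.60 |
| ANCOVA | 1 − ρ² | 0.91 | 0.75 | 0.51 |

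**Step 3: one-sided 5% power at 34 per arm, with 2.1 as the SD of a score.** The ANCOVA residual SD is 2.1√(1 − ρ²) = 2.00, 1.82, 1.50. The change-score SD is 2.1√[2(1 − ρ)] = 2.49, 2.10, 1.63. Simulation of 20,000 trials per setting, with the ANCOVA degree of freedom deducted:

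| Analysis | ρ = 0.3 | ρ = 0.5 | ρ = 0.7 |
|---|---|---|---|
| Mean-score t-test | 89.9% | 89.9% | 89.7% |
| Change-score t-test | 79.3% | 89.9% | 98.3% |
| ANCOVA | 91.9% | 95.6% | 99.3% |

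**Step 4: the same, with 2.1 as the SD of a change.** The score SD becomes 2.1/√[2(1 − ρ)] = 1.77, 2.10, 2.71, and the ANCOVA residual SD is that times √(1 − ρ²) = 1.69, 1.82, 1.94. Normal approximation:

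| Analysis | ρ = 0.3 | ρ = 0.5 | ρ = 0.7 |
|---|---|---|---|
| Mean-score t-test | 96.7% | 90.3% | 73.8% |
| Change-score t-test | 90.3% | 90.3% | 90.3% |
| ANCOVA | 97.8% | 96.0% | 93.9% |

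ANCOVA is the best of the three in every column of both tables. Which t-test comes second depends on ρ.

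**Step 5: chance imbalance.** With a baseline SD of 2.1 (assumed) and 34 per arm, the baseline difference between arms has standard error 2.1 × √(2/34) = 0.51 points. At ρ = 0.5, an imbalance of one standard error moves the mean-score estimate by 0.5 × 0.51 = 0.25 points, and the change-score estimate by 0.25 points the other way, against a target of 1.5. ANCOVA removes this shift in expectation.

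**The case against.** The strongest reply is that unadjusted tests are valid. Under randomisation the t-test keeps its type I error, and its standard error already allows for chance imbalance. Covariates are also commonly left to a fuller protocol or an analysis plan, which is not shown. Both points stand as far as they go: the missing covariate is not an error of validity. But the article does fix its tests, and it fixes the response variable in two ways for the same instruments. Those statements can be improved and reconciled where they are printed.

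Several stronger readings are tempting and should not be drawn:

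- **That the trial is underpowered.** The unadjusted calculation meets its 90% target. If intention-to-treat with carried-forward values keeps all 42 per arm in the analysis, and those values behave like observed ones, the t-test has 94.5% power and ANCOVA 96.1%, 98.2% and 99.8% at the three correlations.
- **That a change score would cost ten points of power.** The 79% needs both ρ = 0.3 and 2.1 as the SD of a score. If 2.1 is the SD of a change, that loss disappears.
- **That the arms are compared by t-tests alone.** Repeated-measures ANOVA is named too, and its interaction term may use the screening score, although not as a covariate.
- **That the mean/change conflict reaches BPI-SF.** The sentence on changes follows WOMAC, M-SACRAH and FACT-B; for BPI-SF only mean scores are stated. For FACT-B the conflict is softer, since the closing phrase on before and after treatment in the Statistical analysis section could be read to cover it as well as BMD.
- **That the scale could be picked after unblinding.** The article blinds the statisticians and withholds assignments until the whole study is complete. It leaves the scale unsettled in print; it does not show that the choice would be made with knowledge of the arms.
- **That leaving out centre is a fault.** Randomization and blinding mentions no stratification by centre, so no stratification factor has been dropped.

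**Conclusion.** The point holds as one of precision and clarity. No baseline adjustment is stated for either named method, although every endpoint has a baseline value. Two sections give different response variables for WOMAC and M-SACRAH, and arguably for FACT-B.

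Over the assumed correlations the power gain over the mean-score t-test is about 2, 6 and 10 percentage points if 2.1 is the SD of a score. If it is the SD of a change, the gain over the change-score t-test is about 8, 6 and 4 points. These sizes rest on the assumed ρ, equal variances at baseline and follow-up, and the planning effect of 1.5. The entry floor on worst pain may narrow the baseline range and lower ρ, which would bring the score-SD figures towards the small end. The change is worth making, but the planned tests are not invalid without it.

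**What to change.** - State one baseline-adjusted analysis per endpoint, in the same words in Quality of life instruments and in Statistical analysis. For BPI-SF, WOMAC, M-SACRAH and FACT-B, use ANCOVA of the follow-up score, or a mixed model over the post-baseline visits, with the baseline score as covariate. For week-12 BMD, use ANCOVA on baseline BMD.
- Report the adjusted mean difference with its confidence interval, and keep the unadjusted t-tests as descriptive or supportive only.
- Say in Sample size calculation whether 2.1 is the SD of a score or of a change.
- Adjustment for centre is optional. If wanted, three hospitals add two terms.

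The cost is wording, plus one degree of freedom per model out of 66 at 34 per arm (three if centre is added). No new data, visits or patients are needed. The change should be dated before the blind is broken.

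Suggested text: *Each questionnaire score will be compared between arms by a model with treatment as factor and the baseline value of the same score as covariate; the adjusted mean difference and its confidence interval will be reported. Week-12 BMD will be analysed in the same way.*
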